#### Intervention Efficacy

The efficacy cluster RCT will use pre- and postintervention data from baseline (T_1_) and follow-up (T_2_ and T_3_) surveys. Data values will be checked for validity (within the appropriate range) using histograms and box plots and corrected whenever possible. Many items are a part of multi-item scales and are anticipated to correlate with each other. Scales will be tested for internal consistency reliability with Swiss and Korean participants using principal component analysis and Cronbach α coefficients. Scales with Cronbach α values of .71 and higher will be used. Multiple imputation or other techniques will address missing data if they exceed 5% of observations and if they are less than 25% for each specific scale. Data from participants who withdraw will be kept to ensure internal validity.

Primary outcomes will be calculated with the Wilcoxon-Mann-Whitney test to compare the proportions of informed relatives per study arm. Other primary and secondary outcomes and metadata from the automatic recording of website activity will be analyzed using descriptive statistics. Descriptive analyses will include calculating the means and frequencies of key variables and subject descriptors (eg, genetic testing). This will include tabulating counts and frequencies of variables, including demographics and personal cancer history. Bivariate analyses (using the chi-square test for differences in proportions and *t* test for differences in means) will assess the associations between demographic factors and clinical characteristics. The following comparisons will be made: between probands and relatives, between men and women, between patients with cancer and cancer-free individuals, between participants with children and those with no children, between different age groups, and between patients with different cancer diagnoses. A detailed methodology for summaries and statistical analyses will be documented in a statistical analysis plan. This plan will be ﬁnalized before database closure and will be under version control at the Clinical Trial Unit, University Hospital Basel. All analyses will be conducted using the statistical software R [71], using *two-sided* statistical tests and conﬁdence intervals with conﬁdence levels α=5% and (100%−α)=95%, respectively. Deviations from planned analyses are not foreseen. The study statistician will review and approve any deviations from the original statistical plan.

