#### Aim 3: Evaluate Intervention Efficacy on Primary and Secondary Outcomes

A cluster RCT will evaluate the magnitude of intervention effects as compared with the comparison website. Randomization will occur at the family level, that is, after baseline data collection, the digital health intervention will randomly assign mutation carriers to either intervention arm, stratifying for country. Invited relatives will be automatically directed to the same arm as the mutation carrier. All study participants will complete a survey at baseline (T_1_) before the intervention and again at 2 months (T_2_) and 6 months (T_3_) after the intervention. The 2- and 6-month follow-up time points will assess the short-term and long-term effects in line with our previous studies [33,50].

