#### Intervention Efficacy

The cluster RCT will invite 114 probands to have a total of 104 evaluable subjects (52 for each website). This sample size would allow detecting whether using the adapted Family Gene Toolkit or the comparison website would increase the proportion of informed relatives by 25% with a statistical power of 80%, a significance level of 5%, and a dropout rate of 9.6% (11/114). We estimated the distribution of the proportion of relatives and dropout rates from our previous studies [14,50]. Less than 10.5% (12/114) of potential participants have no relatives, and less than 10.5% (12/114) have no access to a computer, tablet, or smartphone, making them ineligible for the study. We expect to recruit and retain the final sample of 114 probands over 18 months.

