**Primary outcomes**											
	Proportion of informed relatives	Website data		N/A^a^		N/A		✓^b^		✓	
	Intention to inform relatives	Informing Relatives Inventory [64], 68 items, 7-point Likert scale		.86		—^c^		✓		✓	
	Intention for genetic testing (untested relatives)	1 item, 7-point Likert scale		N/A		N/A		✓		✓	

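### The primary Wilcoxon-Mann-Whitney test is valid, but it uses neither the baseline proportion nor the country stratum, and no effect measure is named

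*Protocol article*

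**What the plan says.** The analysis section (Data Management and Data Analyses, Intervention Efficacy) fixes the primary comparison: "Primary outcomes will be calculated with the Wilcoxon-Mann-Whitney test to compare the proportions of informed relatives per study arm". No covariate, stratum or effect measure accompanies the test. The remaining primary and secondary outcomes are to be described only, so this is the one between-arm inference on efficacy that the article names. The same section says deviations are not foreseen and leaves detailed methodology to a statistical analysis plan that is not shown.

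Three other statements bear on the point:

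- Aim 3 has the system "randomly assign mutation carriers to either intervention arm, stratifying for country", after baseline data collection.
- Table 2 lists "Proportion of informed relatives" as a primary outcome and ticks it at both baseline and follow-up. The analysis section adds: "The efficacy cluster RCT will use pre- and postintervention data from baseline (T_1_) and follow-up (T_2_ and T_3_) surveys". That sentence is not tied to the primary test.
- Aim 3 states the purpose: "A cluster RCT will evaluate the magnitude of intervention effects as compared with the comparison website". The sample-size paragraph asks whether either website "would increase the proportion of informed relatives by 25" per cent. The analysis section also plans 95% confidence intervals in general terms, without saying for which quantity.

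**The concern.** A proband who has already told most relatives at T1 will probably still show a high proportion at follow-up. If the outcome counts everyone informed so far, the follow-up value contains the baseline value. Much of the spread between probands would then be fixed before randomisation, and an unadjusted test treats that spread as noise. With 52 probands per arm, a chance difference in T1 disclosure would also carry over into the observed difference between arms.

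A rank test by itself yields a p-value. The trial is designed around an increase of a stated size, so readers will want an estimate on that scale with an interval, and the article does not say which estimate they will get.

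**Working it through.** **The plan's own figure.** The inputs are 52 evaluable probands per arm, 80% power and 5% significance (Sample and Sample Size, Intervention Efficacy), with two-sided tests (analysis section). The 104 cannot be re-derived, because the article gives no control proportion, no standard deviation (SD), and does not say whether the 25% is absolute or relative. Solving backwards for an absolute difference of 0.25:

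- SD = 0.25 × √(52/2) / (1.960 + 0.842) = 0.25 × 5.099 / 2.802 = 0.455 for a normal-theory test.
- With the Wilcoxon efficiency of 3/π, SD = 0.455 × √0.955 = 0.445.

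The check below therefore takes 80% power for the unadjusted test as given.

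**Gain from the T1 proportion.** Adjusting for a baseline value with correlation ρ reduces the SD to SD × √(1 − ρ²). The efficiency factor cancels, so power = Φ(2.802/√(1 − ρ²) − 1.960), and 80% power needs 52 × (1 − ρ²) per arm. The documents give no ρ, so the values are assumptions.

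| ρ | 2.802/√(1 − ρ²) | Power | Per arm for 80% |
|---|---|---|---|
| 0 | 2.802 | 80.0% | 52 |
| 0.2 | 2.859 | 81.6% | 50 |
| 0.3 | 2.937 | 83.6% | 48 |
| 0.5 | 3.235 | 89.9% | 39 |
| 0.6 | 3.502 | 93.8% | 34 |
| 0.7 | 3.923 | 97.5% | 27 |

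**Chance imbalance.** With equal SDs, a baseline imbalance of one standard error is SD × √(2/52). It shifts the unadjusted follow-up difference by ρ times that. The effect detectable with 80% power is 2.802 × SD × √(2/52). The shift is thus ρ/2.802 of that effect: 11% at ρ = 0.3, 18% at 0.5 and 25% at 0.7.

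**Simulation.** 1,500 trials were run per setting, with 52 probands per arm, 2 to 10 relatives each, beta-binomial proportions and a 25-point difference (0.375 against 0.625). These settings are assumptions.

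- Type I error of the unadjusted Wilcoxon test was 3.6% to 5.5%.
- Its power was 87% to 88%. Rank ANCOVA on T1 proportion and country had 92% to 93% at an observed correlation of about 0.4 and 98% at about 0.66. With no correlation and no country difference the two were equal.
- With a 20-point country difference, stratifying the Wilcoxon test by country (van Elteren) moved power from 86.9–88.2% to 88.1–89.5%, about 1 point.

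**Why ρ may be large.** If the proportion is cumulative, a proband with baseline share b who tells a fraction q of the uninformed relatives ends at b + q(1 − b) = q + (1 − q)b. Follow-up then depends on baseline with slope 1 − q, for example 0.8 when q is 20%.

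**The case against.** The strongest reply is that nothing here is an error. Families are randomised, each proband contributes one proportion, and the rank test holds its type I error. Chance imbalance is already allowed for in the p-value. Covariates and effect measures are ordinary content of a statistical analysis plan, one is promised, and the article says that pre- and postintervention data will be used. Validity stands in full. The deferral stands in part: the plan may add detail, but the article itself names the primary test, and adding adjustment would change that named method.

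A reader might infer that the trial is underpowered. The documents do not support that. Simulating a cumulative outcome with half the relatives informed at T1, and 20% against 45% of the rest then told, gives 45–54% power unadjusted against about 99% adjusted. But that is a difference of only 0.5 × (0.45 − 0.20) = 12.5 points. At 20% against 70%, which is 25 points, the unadjusted test has 97–99.6% power.

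The size of the gain also depends on a definition the article does not give. If the outcome were the share of previously uninformed relatives who were then told, simulation gives no baseline correlation. The unadjusted test (97–98%) is then slightly better than the adjusted one (95–97%).

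Two further inferences go too far. One is that no effect size will be estimated: confidence intervals are planned and the magnitude of effect is the stated aim, so the measure is unnamed rather than excluded. The other is that ignoring country makes the test unsafe. Under an assumed 30-point country difference its size falls to about 2–4%, which is conservative.

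**Conclusion.** The point holds as a free improvement. The named primary test is valid but leaves out a baseline measure of the same outcome and the stratification factor, both already available, and the primary comparison has no named effect measure. Taking 80% power for the unadjusted test as given, the efficiency forgone runs from nothing at ρ = 0 to about 10 points at 0.5 and 17.5 points at 0.7. Nearly all of it comes from the T1 proportion. These figures rest on assumed correlations. A substantial correlation is likely if the proportion is cumulative, which is the natural reading but is not stated. No shortfall from 80% and no inflation of type I error has been shown.

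**What to change.** Make the primary analysis a proband-level model of the follow-up proportion on arm, T1 proportion and country, with robust standard errors, or a rank ANCOVA on the same terms. Report the adjusted difference in mean proportion with its 95% confidence interval, so that the result can be set beside the 25% target. Keep a Wilcoxon test stratified by country (van Elteren) as a sensitivity analysis. State whether the proportion is cumulative, because the value of the baseline covariate depends on it.

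The cost is wording in the protocol and the statistical analysis plan, which the article says will be finalised before database closure. Every variable is already collected, and no further participants are needed.

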### Objectives

The DIALOGUE study will build a bilateral research infrastructure to support collaboration and multidisciplinary initiatives around HBOC in Switzerland and Korea. The specific aims are to develop the K-CASCADE (Korean–Cancer Predisposition Cascade Genetic Testing) cohort in Korea by expanding an existing research infrastructure developed by the CASCADE Consortium in Switzerland; develop a digital health intervention to support open communication and cascade genetic testing in HBOC families, based on the linguistic and cultural adaptation of the Family Gene Toolkit; evaluate the efficacy of the digital health intervention on primary (communication of genetic test results to relatives and cascade genetic testing) and secondary (psychological distress, genetic literacy, coping, and decision making) outcomes; and explore the translatability of the platform using the reach, effectiveness, adoption, implementation, and maintenance (RE-AIM) framework.

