#### Intervention Efficacy

Data to evaluate the magnitude of intervention effects will be assessed using the instruments listed in Table 2. These have strong psychometric properties and have been used in previous studies on patients with cancer. Most of these instruments have been translated into and validated in German, French, and Italian and will be translated into and validated in Korean. Primary and secondary outcomes are assessed at the 2-month and 6-month follow-up surveys. Satisfaction with the intervention and acceptability will be assessed at the 2-month follow-up with questions about intervention usefulness, ease of use, clarity, appropriate length, level of detail, relevance, and interest with a 7-item survey (Likert scale ranging from 1=low to 7=high) [62,63].

**Table 2 table2:** Instruments to assess primary and secondary outcomes.

Concepts			Instruments		Cronbach α		Test-retest reliability		Assessment		
									Baseline		Follow-up

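### Two of the three primary outcomes and all six secondary outcomes have no planned comparison of the randomised arms, although the efficacy aim covers them

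*Protocol article*

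**What the plan says.** The Objectives undertake to "evaluate the efficacy of the digital health intervention on primary (communication of genetic test results to relatives and cascade genetic testing) and secondary" outcomes, the secondary ones being distress, genetic literacy, coping and decision making. Aim 3 fixes the contrast: "A cluster RCT will evaluate the magnitude of intervention effects as compared with the comparison website". The Intervention Efficacy part of Measures and Outcomes ties the instruments to that purpose: "Data to evaluate the magnitude of intervention effects will be assessed using the instruments listed in Table 2".

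Table 2 lists three primary outcomes: "Proportion of informed relatives", "Intention to inform relatives", and the intention of untested relatives to have genetic testing. It lists six secondary measures. All nine are marked for baseline and follow-up.

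The Intervention Efficacy part of Data Management and Data Analyses gives a Wilcoxon-Mann-Whitney test between arms for the proportion of informed relatives. It continues: "Other primary and secondary outcomes and metadata from the automatic recording of website activity will be analyzed using descriptive statistics". It explains descriptive analysis as means, counts and frequencies. Chi-square and t tests are then assigned to associations between demographic and clinical characteristics, with the list: "The following comparisons will be made: between probands and relatives, between men and women, between patients with cancer and cancer-free individuals", followed by having children or not, age group and cancer diagnosis.

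**The concern.** The aim is causal and comparative, and it covers all the outcomes. The analysis is comparative for one of them. Two outcomes carry the label primary but are given no arm comparison. One of these two, intention for testing among untested relatives, is the only primary outcome in Table 2 that represents cascade testing, which the Objectives name as half of the primary aim.

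If the text is followed, the report could give an effect estimate for communication to relatives. For testing intention, distress, literacy, coping and decision making it would give summaries that support no statement about the intervention's effect. If arm contrasts were first added in the SAP, which need only be final before database closure, they would depart from the published analysis and have no public prespecification.

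**Working it through.** **Step 1. Set promise against analysis.** Outcomes are the primary and secondary rows of Table 2; the last column comes from the data analysis section.

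| Table 2 outcome | Label | Arm comparison named |
|---|---|---|
| Proportion informed | Primary | Yes, Wilcoxon-Mann-Whitney |
| Intention to inform | Primary | None, descriptive |
| Testing intention, untested relatives | Primary | None, descriptive |
| Distress | Secondary | None, descriptive |
| Literacy: genetic affinity | Secondary | None, descriptive |
| Literacy: cancer genetics | Secondary | None, descriptive |
| Coping | Secondary | None, descriptive |
| Decisional conflict (untested) | Secondary | None, descriptive |
| Decisional regret (tested) | Secondary | None, descriptive |

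Count: 3 + 6 = 9 outcomes, of which 1 has an arm comparison and 8 do not (2 of 3 primary, 6 of 6 secondary).

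**Step 2. Look for another sentence that fills the gap.** The chi-square and t tests cover six comparisons, and study arm is not among them. The sentence on two-sided tests and 95% confidence intervals names no contrast. The Wilcoxon sentence opens with primary outcomes in the plural but limits itself to the proportion informed, and the next sentence moves the other primary outcomes to descriptive analysis.

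**Step 3. The plan's own sample size.** It gives 104 evaluable probands, 52 per arm, for a 25% increase in the proportion informed at 80% power and 5% significance. The distribution used is not stated, so 52 cannot be reproduced uniquely. Taking 25% as 0.25 on the proportion scale, the SD that gives 52 per arm is

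0.25 / [(1.960 + 0.842) × √(2/52)] = 0.455,

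or about 0.445 with the Wilcoxon efficiency factor π/3. The stated figure is plausible, neither confirmed nor refuted. No calculation covers any other outcome.

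**Step 4. What an arm contrast would give at 52 per arm.** For a proband-level outcome in SD units, without baseline adjustment:

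- 95% CI half-width: 1.960 × √(2/52) = 0.38 SD.
- Detectable difference, two-sided 5%, 80% power: (1.960 + 0.842) × √(2/52) = 0.55 SD.
- The same with three primary outcomes at 0.05/3 each: (2.394 + 0.842) × √(2/52) = 0.63 SD.
- Familywise error for three independent tests at 5%: 1 − 0.95³ = 14.3%.

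These figures do not apply to testing intention. That outcome is measured in untested relatives, whose number in the trial is not given and whose answers are clustered by family.

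**Step 5. Baseline adjustment.** With correlation r between baseline and follow-up, variance falls by r². The documents give no r. Assuming 0.5 to 0.7, the reduction is 25% to 49%, and the half-width becomes 0.38 × √(1 − r²), that is 0.33 SD (r = 0.5) to 0.27 SD (r = 0.7).

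**The case against.** Three points on the other side deserve weight.

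- **The SAP is not shown and is to hold the detailed methodology.** Model form, covariates and random effects do belong there, and their absence is no fault. But the article is not silent on these outcomes: it states a descriptive analysis. Adding arm contrasts would change that statement, and the same section foresees no deviations from the planned analyses.
- **Formal testing only of the outcome on which the trial was sized is defensible.** It limits multiplicity, and no power was calculated for anything else. This stands as a reason not to make the other contrasts confirmatory. It does not justify omitting an estimate with an interval, or calling two outcomes primary without comparing them between arms.
- **Nothing forbids tabulating the descriptive statistics by arm, and the section mentions 95% confidence intervals.** That is true, and an unadjusted difference could be worked out from such tables. No arm difference or interval for it is stated, however, and arm-wise summaries alone do not give the magnitude of effect that Aim 3 promises.

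A reader might go further and infer that the efficacy aim cannot be answered at all. The documents do not support that: the proportion informed is a listed primary outcome, is the one the trial was sized on, and is tested between arms. A reader might also infer that the baseline values go unused. The data analysis section says that pre- and postintervention data will be used; what is missing is an adjusted arm contrast.

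**Conclusion.** The point holds for eight of the nine primary and secondary outcomes in Table 2. The efficacy aim is answered only for the proportion of informed relatives; the cascade-testing half of the primary aim has no planned arm contrast. This is a contradiction within the article, between its Objectives, Aim 3 and measures text on one side and its analysis text on the other.

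The conclusion rests on the wording and needs no numerical assumption. The precision figures are illustrative: they assume 52 evaluable probands per arm and a proband-level outcome on a standardised scale. Any gain from baseline adjustment depends on a correlation that the documents do not give.

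**What to change.** Replace the sentence that assigns the other outcomes to descriptive statistics. State that each remaining Table 2 primary or secondary outcome is reported as a between-arm difference with a 95% confidence interval at T2 and T3, adjusted for its T1 value and for country (the stratification factor), with allowance for family clustering where relatives contribute. The exact model can be left to the SAP.

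Label these contrasts secondary or exploratory, and change the primary label of the two intention outcomes in Table 2 to match. If they are to stay primary, multiplicity has to be addressed. The alternative is to narrow the efficacy aim, wherever it appears, to the proportion informed.

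The cost is a text change and modest programming, with no new data. The downside is that the added estimates will be imprecise (about ±0.38 SD before adjustment for proband-level outcomes), so a wide interval should not be read as absence of effect.

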#### Intervention Translatability

Data exploring the RE-AIM of the digital health intervention will be analyzed using qualitative and quantitative methods. Narrative data obtained from mini-interviews will be audiorecorded, transcribed verbatim, and analyzed for common themes. Descriptive analyses will include calculating the means and frequencies of the key variables and subject descriptors. Bivariate analyses (chi-square test for differences in proportions and *t* test for differences in means) will compare key variables between participants and nonparticipants.

## Results

The DIALOGUE study, including the development of the K-CASCADE cohort in Korea, was funded in October 2019. It is projected that data collection will be completed by January 2023, and results will be published in fall 2023.

## Discussion

### Principal Findings

The need to enhance family communication around HBOC has been documented in the literature since mid-2000 [72-74], followed approximately 10 years later by scientific calls to enhance cancer predisposition cascade genetic testing [75-77]. The DIALOGUE study is a resource-effective international research platform that proposes building a tailored, interactive website to reach a large number of HBOC families and enhance cancer predisposition cascade genetic screening, presumably requiring only a fraction of the cost and required clinician time compared with previous approaches. Developing the K-CASCADE cohort will link together the expertise of an eminent network of HBOC scholars and clinicians that will benefit both countries and serve as a model for potential expansion to other countries and in other language contexts. The cross-cultural adaptation of the Family Gene Toolkit will help explore the similarities and differences in communication practices among HBOC families in the Swiss and Korean contexts, potentially providing important information about the Korean and Swiss contexts that affect HBOC discourse [78]. This comparison will also reveal context-specific characteristics regarding the influence of the health care system, insurance coverage, and socioeconomic aspects on the application of genetic knowledge that can provide useful information for adapting other digital health solutions within the Swiss and Korean contexts. The goal of the adapted Family Gene Toolkit is to attend to the needs of diverse families, including the function of different members, and cultural and linguistic backgrounds. It is thus important to consider digital health technologies as sociocultural products with a need for an adaptation to specific local contexts and a critical reflection about how they may affect local perceptions of illness [78]. The final product will likely be more cost-effective and will expedite scaling-up, dissemination, and implementation, given the existing strong clinical partnerships within each country.

